**Methods:**

The effects of the intervention on reduction in excess body weight (primary outcome), hemoglobin A1c, blood pressure, and changes in lifestyle behaviors associated with weight trajectory and T2DM risk in mother-child dyads will be evaluated during a 13-week, group randomized trial wherein 60 mothers and their children will be recruited to the intervention or wait-listed control conditions at one of two FQHC locations. Intervention participants (*n* = 30) will begin the group program immediately, whereas the wait-listed controls (*n* = 30) will receive a booklet describing self-guided strategies for behavior change. Associated program delivery costs, acceptability of the program to participants and FQHC staff, and potential for long-term sustainability will also be evaluated.

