**Fig. 1 Fig1:**
[figure not shown]
EPIC El Rio Families Participant Anticipated Enrollment and Study Design

This design is responsive to standards of care for T2DM prevention [44] and will provide the opportunity to investigate pre−/post-intervention effects, intervention versus control effects, and maintenance effects. The number of participants and design also allow us to evaluate processes critical to successful implementation by El Rio, informing future replication and the potential scaling of the intervention to other sites in this and other FQHC networks. This clinical trial (ClinicalTrials.gov identifier NCT03781102) has been approved by the University of Arizona Institutional Review Board and all participants will provide informed consent or assent prior to participation.

Changes in percent weight for the mothers and changes in the BMI z-score for the children are used to confirm that there is adequate statistical power with the sample size of *n* = 60 dyads. For mothers, the calculation is based on the observed change in the DEPLOY study for both sexes [34]. The mean change in body weight after 6 months was − 6.0% (standard deviation = 4.0%). For children, the calculation is based on data from the EPIC Kids Study in which the mean change in BMI z-score was 0.054 (standard deviation = 0.02) [32]. The power calculation assumed that in each period (intervention versus wait-list control) there will be 3 groups with 10 dyads per group (*n* = 30 intervention versus *n* = 30 wait-list control). The statistical power is > 80% for the mothers and 95% for the children assuming an intra-group correlation or 0.15 or below (two-sided alpha level of 0.05). As this is a pilot study to provide estimates for a larger trial, there is no adjustment for multiple comparisons.

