The primary outcome is percent change in body weight and BMI at 13 weeks (post-intervention) and 26 weeks (follow-up/weight maintenance). Body weight and height will be measured using a calibrated, digital scale with a mechanical height rod and a stadiometer. Adult BMI is categorized using international classifications of BMI (overweight, 25–29.9 kg/m^2^; obese, > 30 kg/m^2^) [45]. In children, BMI percentile is determined using age- and sex-specific growth charts developed by the CDC in 2000 [46]. Lacking a gold standard for measuring change in weight status in children, we will use the recommended BMI z-score change, which has been established as a good proxy for fat mass z-score change [47]. Child and adult waist circumference, linked to metabolic syndrome in both populations, will be measured at the umbilicus. All measures will be completed in duplicate, and the average of the two measures will be used. Secondary physiological outcomes in children and mother**s** include changes in blood pressure and hemoglobin A1c (HbA1c). These data will be collected using portable, CLIA approved technologies. The definition of hypertension will be adjusted for age per national guidelines [48, 49].

.

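### Week 26 shares primary status with week 13 although the controls are by then treated, so the primary result may average two different contrasts; the primary endpoints should be named by population and fixed at week 13

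*Protocol article*

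**What the plan says.** All places are in the protocol article.

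- **Abstract, Methods:** the primary outcome is "reduction in excess body weight (primary outcome". The term is not defined there and is not used again.
- **Evaluation section, outcome paragraph:** "The primary outcome is percent change in body weight and BMI at 13 weeks (post-intervention) and 26 weeks (follow-up/weight maintenance". No population is attached to this sentence. Later in the paragraph, for children, "we will use the recommended BMI z-score change".
- **Evaluation section, sample-size paragraph:** "Changes in percent weight for the mothers and changes in the BMI z-score for the children are used to confirm" that 60 dyads suffice. The test level is a "two-sided alpha level of 0.05". The paragraph ends: "As this is a pilot study to provide estimates for a larger trial, there is no adjustment for multiple comparisons".
- **Evaluation section, randomisation paragraph:** after 13 weeks the intervention arm moves to follow-up and the wait-list arm starts the programme.
- **Evaluation section, analysis paragraph:** a mixed-model analysis of covariance covers both times. The time-by-group interaction is assessed first. If it is absent, one treatment difference over both times is assessed; if it is present, the difference is assessed at each time.

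**The concern.** The between-arm contrast means different things at the two primary time points. At week 13 it compares families who had the programme with families who had not. At week 26 it compares families 13 weeks past the programme with families who have just finished it. If the programme works, the second contrast should be smaller than the first and could vanish. It could even reverse if the intervention arm regains weight.

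The article gives both times equal standing and lets a test on the data decide whether they are pooled. The headline estimate could therefore be the week-13 effect, or an average of that effect and a treated-versus-treated difference. This matters for a pilot whose stated purpose is to supply estimates for a larger trial, because a diluted estimate would carry through to its sample size. The loose wording adds to the problem: the abstract names a different, undefined primary outcome, and the primary sentence leaves the reader to work out which measure belongs to whom.

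**Working it through.** **1. The plan's own power figure.** Inputs from the sample-size paragraph: 3 groups of 10 dyads per arm, intra-group correlation 0.15, mothers' change −6.0% with SD 4.0%, two-sided 0.05.

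- Design effect = 1 + (10 − 1) × 0.15 = 2.35.
- Effective n = 30 / 2.35 = 12.77 per arm.
- Standard error = 4.0 × √(2 / 12.77) = 1.58.
- Power = 96.6% by the normal approximation, or 80.6% by a t test on 4 df (6 groups − 2).

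Both agree with the stated figure of more than 80% for mothers. For children (0.054, SD 0.02) the t test on 4 df gives 99.8%; the article says 95%, which fits only if read as at least 95%.

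**2. What pooling does.** Let d13 and d26 be the between-arm differences, and c = d13 − d26 the amount by which the controls catch up. With equal weight on the two times (an assumption):

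pooled difference = (d13 + d26) / 2 = d13 − c/2.

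If the plan's 6.0% is taken as d13, the pooled value lies between 6.0 (no catch-up) and 3.0 (full catch-up).

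**3. Whether the interaction test would prevent this.** The interaction contrast is c. Its standard error is SD × √(2(1 − ρ)) × √(2/n), where ρ is the correlation between the two changes. The article gives no ρ, so I assume 0.7 to 0.8. I also apply the design effect of 2.35 to this contrast.

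- ρ = 0.7: 4.0 × √0.6 × √(2/12.77) = 1.23.
- ρ = 0.8: 4.0 × √0.4 × √(2/12.77) = 1.00.

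Chance that the test detects c:

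| Catch-up c (percentage points) | ρ = 0.7: normal / t, 4 df | ρ = 0.8: normal / t, 4 df | Dilution if missed (c/2) |
|---|---|---|---|
| 2 | 37% / 24% | 52% / 34% | 1.0 |
| 3 | 69% / 46% | 85% / 62% | 1.5 |
| 6 | 99.8% / 95% | above 99% / 99% | 3.0 |

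Complete catch-up from a 6-point effect would almost always be detected. Partial catch-up, or full catch-up from a smaller effect, often would not. A non-significant interaction is therefore weak evidence that the two contrasts agree.

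**4. Size of the primary family.** In mothers, at constant height, percent change in BMI equals percent change in weight, because the height term cancels. Children have one measure, the z-score. That leaves about 2 populations × 2 times = 4 tests.

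- As written: 1 − 0.95⁴ = 18.5% under independence. With assumed correlations (mother–child 0 to 0.5, week 13–week 26 0.7 to 0.8), simulation gives about 14 to 16%.
- With two week-13 endpoints: 1 − 0.95² = 9.75% under independence.

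**The case against.** The best defence is that the article, read as a whole, is clearer than its primary sentence. The sample-size paragraph pairs percent weight with mothers and BMI z-score with children, and the outcome paragraph repeats the z-score choice. Week 26 is labelled as maintenance, and the design rationale lists maintenance apart from the intervention-versus-control effect. The interaction test does give some protection. No success criterion is set, and the study is declared a pilot.

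Much of this stands, and it rules out several stronger readings that a reader might infer:

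- **Percent weight change will be analysed in growing children.** The outcome paragraph specifies BMI z-score change for them.
- **The primary outcome has three rival definitions.** The sample-size paragraph is a power basis and is not labelled primary. Only the abstract and the outcome paragraph carry that label.
- **There are eight primary tests with a 34% error rate** (1 − 0.95⁸). That count includes percent weight in children and counts mothers' weight and BMI twice.
- **A multiplicity correction has been overlooked.** The article states that there is none and gives the reason.

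The defence does not dispose of the week-26 problem. The maintenance label does not remove week 26 from the primary outcome, and the analysis paragraph still pools it with week 13 as a between-arm difference. Nor does pilot status say which estimate the larger trial should use.

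**Conclusion.** The point holds in a limited form. Week 26 should not share primary status with week 13, because its between-arm contrast has no untreated comparator and may be pooled into the headline estimate. The pooled estimate is probably diluted, by half the controls' catch-up: about 1.0 to 1.5 percentage points for a catch-up of 2 to 3 points. This rests on equal weighting of the two times, the assumed correlations of 0.7 to 0.8, and the article's SD and intra-group correlation. The direction rests on the programme also working in the control arm. The undefined abstract term and the unassigned primary sentence are genuine inconsistencies, but they are matters of wording. The lack of multiplicity adjustment is a declared choice and is not a fault here.

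**What to change.** - State two primary endpoints: mothers' percent change in body weight and children's change in BMI z-score. Define both as the between-arm contrast at week 13, not an average over time points.
- Make mothers' BMI and all week-26 (maintenance) results secondary. The mixed model can stay, but the primary estimate should be its week-13 contrast whatever the interaction test shows.
- Replace the abstract's primary outcome with the same two endpoints, or define the term in a way that agrees with them.
- Keep the statement that no multiplicity adjustment is made.

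The cost is wording in the abstract, the outcome paragraph and the analysis paragraph. No data or participants are added. The two measures are those the trial was sized on, and each is still tested at 0.05, so the step 1 power for mothers is unchanged on the article's inputs. One caution remains: the mothers' 6.0% is a 6-month value, so that power carries over to week 13 only if a similar effect is reached by then.

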### Evaluation of the *EPIC El Rio Families* Study

This study uses a group randomized design to compare two groups of mothers who have had GDM or have been diagnosed with prediabetes, along with their children, who are between 8- and 12-years-old. The goal is to recruit 60 mother/child dyads to either the EPIC El Rio Families intervention or wait-listed control conditions. To identify potential participants with histories of GDM and/or prediabetes who are patients at El Rio, we will query the FQHC’s electronic health record (EHR). Women with a history of GDM during any of their pregnancies and/or a prior diagnosis of prediabetes and who have children 8- to 12-years-old at time of study will be contacted by phone and mail and invited to participate in *EPIC El Rio Families*. The participating child must be a biological child but does not have to be the direct product of a pregnancy with GDM. With attention to the composition of the FQHC patient population, the study sample will reflect majority Hispanic women from lower income groups.

Two El Rio clinics (A and B) have been selected to participate in this pilot study. Randomization to the intervention and wait-list control conditions will be performed *by site* using flip of a coin. Randomization by site has the least potential for contamination during the initial delivery period. Upon confirming respondent eligibility and obtaining written informed consent/assent, the research coordinator will match participants to the intervention site geographically nearest to their home, assign a study ID, and schedule baseline measurements. Following measurements, intervention participants will begin the 13-week face-to-face group program immediately, whereas the wait-listed controls will receive information about the offer to participate in the intervention after the first implementation and that they will continue to receive standard of care including access to nutritional counseling if desired. After 13 weeks, the intervention participants will transition to a follow-up phase while the wait-listed controls will begin the intervention (Fig. 1). Blinding is not possible with this design.

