Secondary behavioral outcomes associated with weight trajectory and T2DM risk in children and mothers will be assessed at 13 weeks (post-intervention) and 26 weeks (follow-up/weight maintenance). Child dietary intake will be assessed with *two, nonconsecutive*, interviewer-administered *24-h dietary recalls* conducted telephonically by trained nutritionists and entered into the Nutrient Data System for Research (Minneapolis, MN, v. 2012) [50]. Overall diet quality and its components (total vegetables, whole fruit, whole grains, plant, animal, and seafood proteins, fats, sodium, sugar, and refined grains) will be calculated using the Healthy Eating Index-2015, a valid and reliable measure of diet quality designed to assess the degree to which an individual’s intake conforms to dietary recommendations [51, 52]. Child moderate to vigorous physical activity and sedentary behavior will be assessed using the *Youth Activity Profile,* a self-administered 7-day (previous week) recall questionnaire validated for use in children ages 8- to 12-years-old [53] that includes 15 items divided into three sections: activity at school, activity out-of-school, and sedentary. Sleep behavior will be assessed using the *Children’s Sleep Habits Questionnaire, Abbreviated*, a 22-item survey designed for parent report of key child sleep domains that encompass major medical and behavioral sleep disorders in school-aged children [54]. Maturity will be assessed from a self-report of Tanner’s breast/genital and pubic hair descriptions. The validated questionnaire presents illustrations of developmental stages shown to agree with pubertal staging by a physician [55].

Parental dietary intake will be assessed using the validated *Arizona Food Frequency Questionnaire*, a self-administered semi-quantitative 159-item questionnaire in which respondents report how often they typically consume specific foods and food groups and associated portion sizes in the past 3 months [56, 57]. Parent physical activity will be assessed using the validated *Arizona Activity Frequency Questionnaire*, a self-administered 59-item questionnaire in which participants report whether they performed each activity during the past 28 days [58]. Primary outputs include daily energy expenditure (kilocalories), number of hours per day spent in each activity, and number of activities reported for each category.

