The home food and physical activity environment will be assessed using the *Family Nutrition and Physical Activity Tool,* a 21-item survey of the family home environment and practices associated with children’s risk of becoming overweight. Parents will use the tool to report the frequency of breakfast and family meals, modeling of nutrition, nutrient dense foods and high calorie beverages, restriction and reward, parent modeling physical activity, child’s physical activity, screen time, TV in bedroom, and sleep routines [59, 60].

Given the considerable impact of social and environmental factors on participants’ ability to follow through with health recommendations, we will collect demographic and socioenvironmental data associated with T2DM risk and health disparities (e.g., food insecurity, housing stability, culture and language, community support, socioeconomic status, financial barriers, literacy and numeracy) using the PRAPARE questionnaire developed for use in health care settings, and already routinely implemented by El Rio. All surveys will be made available in English and Spanish.

The intention-to-treat principle will be used for all the analyses. Differences in participants’ baseline characteristics between the two groups will be evaluated by a two-sample *t*-test for continuous outcomes and by Chi-square test or Fisher’s exact test for categorical outcomes. Initial analyses will compare the changes between baseline and follow-up between the intervention versus wait-list control groups using two-sample sample *t*-tests. Subsequently, a mixed-model analysis of covariance including treatment group, time, and baseline value of the outcome will be used to assess the effects of intervention at 13 and 26 weeks. Participants will be treated as a random effect nested within group. An interaction effect between time and treatment group will be assessed first. If there is no interaction effect, the overall treatment difference will be assessed. Otherwise, the treatment difference will be assessed at each time point. In order to measure the relative cost-effectiveness of these programs, we will also explore costs associated with implementation by El Rio staff.

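### The stated child model adjusts only for the outcome's own baseline, although maturity, age and sex are recorded and the clinic-based allocation does not balance them

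*Protocol article*

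**What the plan says.** All of the following is in the protocol article, section Evaluation of the EPIC El Rio Families Study.

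- **Allocation.** Two clinics are assigned to the two conditions by coin flip, one clinic per arm. The coordinator will "match participants to the intervention site geographically nearest to their home".
- **Maturity.** In the paragraph that opens with the secondary behavioral outcomes at 13 and 26 weeks: "Maturity will be assessed from a self-report of Tanner’s breast/genital and pubic hair descriptions". No use of the score in the analysis is given.
- **Child weight outcome.** "we will use the recommended BMI z-score change, which has been established as a good proxy for fat mass z-score change". For the reference charts, "BMI percentile is determined using age- and sex-specific growth charts developed by the CDC in 2000". Age and sex must therefore be on record for every child.
- **Other child outcomes.** Waist circumference, blood pressure, HbA1c, diet, activity and sleep are measured. Only the definition of hypertension is said to be adjusted for age.
- **Analysis.** Unadjusted t-tests on changes come first, then a "mixed-model analysis of covariance including treatment group, time, and baseline value of the outcome", with this random part: "Participants will be treated as a random effect nested within group". Baseline characteristics are compared between arms by significance tests, but no result of those tests leads to adjustment.

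**The concern.** Children of 8 to 12 differ widely in age and pubertal stage. Growth common to both arms cancels in the comparison, but a difference between the two clinics' children in age, sex or stage does not. With individual randomisation such a difference would be chance alone, and the standard error would allow for it. Here children reach an arm through where they live, so a systematic difference is possible and the stated model has no term for it beyond the outcome's own baseline.

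The baseline value does part of the work, since it absorbs differences in starting level. It does not absorb different expected change from the same starting level, which is what maturity could bring over 13 to 26 weeks. The initial t-tests on change have no covariate at all.

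At stake are mainly the child secondary outcomes analysed on raw scales. The study is described as a pilot supplying estimates for a larger trial, so an avoidable distortion would be carried forward.

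**Working it through.** **1. Does a stated figure turn on this?** No. The nearest is the children's power of 95% (change 0.054, SD 0.02, 30 per arm in groups of 10, intra-group correlation 0.15). Design effect 1 + (10 − 1) × 0.15 = 2.35; effective n = 30 / 2.35 = 12.77 per arm. Power is above 99.9% by normal approximation, or 99.8% by noncentral t with 4 degrees of freedom (6 groups − 2). The stated 95% is not reproduced, but that is a separate matter. For this point, cutting the residual variance by up to 20% leaves the normal-approximation power above 99.9%, so on the plan's own inputs a covariate has no material power to add for BMI z-score.

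**2. Which child outcomes are exposed?**

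| Child outcome | Standardised for age and sex in the text? | What a clinic difference could carry |
|---|---|---|
| BMI z-score change | Yes | Pubertal timing relative to age and sex |
| Waist circumference | Not stated | Age, sex, maturity |
| Blood pressure, continuous | Not stated (age adjustment is for the hypertension definition) | Age, sex, maturity |
| HbA1c | Not stated | Age, sex, maturity |
| Activity | Not stated | Age, sex, maturity |

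**3. Size of bias.** Bias = (slope of change on maturity, given baseline) × (difference in mean maturity between clinics). The documents give neither factor, so what follows is illustration only.

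- *In SD units.* Assume a correlation r of 0.2 to 0.4 with the change, after allowing for baseline, and a difference of 0.5 SD. Bias = 0.5 × r = 0.10 to 0.20 SD of the change.
- *BMI z-score, planning SD 0.02.* 0.10 × 0.02 = 0.002 and 0.20 × 0.02 = 0.004, which is 3.7% and 7.4% of 0.054.
- *Wider grid.* Slopes of 0.005 to 0.05 z per stage and differences of 0.25 to 1.0 stage give 0.00125 to 0.05 z, or 2% to 93% of 0.054. The upper end does not fit the plan's own SD. If stage has an SD of about 1 (assumed), r = slope / 0.02, so a slope of 0.02 already means r = 1 and 0.05 is impossible. If the true SD of change exceeds 0.02, larger slopes become possible.

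**4. Would the planned baseline tests catch it?** With 30 per arm, treated as independent, the standard error of a standardised mean difference is √(2/30) = 0.26 SD. A 0.5-SD difference is 0.5 / 0.26 ≈ 1.9 standard errors, and a two-sided 5% t-test has about 48% power to detect it. It would be missed about half the time, and a positive test triggers nothing in the text.

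**5. Precision.** Residual variance falls by r². Equivalent sample size = 60 / (1 − r²), ignoring clustering:

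| r | r² | Equivalent N | Gain |
|---|---|---|---|
| 0.2 | 0.04 | 62.5 | 2.5 children |
| 0.3 | 0.09 | 65.9 | 5.9 children |
| 0.4 | 0.16 | 71.4 | 11.4 children |

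Against a cost of about three degrees of freedom, there is no net gain at the low end.

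**The case against.** The strongest reply is that this is one sentence in a condensed article, that its list of terms need not be exhaustive, and that outcome-specific covariates are commonly settled in an analysis plan not shown here. That stands to this extent: the right description is that maturity, age and sex are not named in the stated model, not that the sponsor has decided against them. The point survives because the article does more than stay silent. It states a single model for mothers and children, names its one adjustment covariate, and collects maturity without a role.

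Four stronger readings are tempting and are not supported.

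- *Growth differences distort the child weight outcome.* BMI z-score already removes age and sex, and only timing relative to them is left.
- *Maturity will be tested as an intervention effect.* It is described in the paragraph on secondary behavioral outcomes, but no sentence announces such a test. Only its placement is unhelpful.
- *The study loses meaningful precision.* The gain is small and may be nil.
- *A bias of a given size is present.* The correlations and the 0.5-SD imbalance are assumptions, and nothing shows that two clinics of one health centre differ that much.

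It can also be said that maturity is only one of many ways the clinics may differ, and that with one clinic per arm no covariate separates treatment from clinic. That is correct and limits what the change can achieve. It is no reason to leave a measured and plausible confounder unused.

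**Conclusion.** The point holds as a modest improvement to the stated analysis. The model names only treatment group, time and the outcome's baseline, and the allocation leaves children's maturity, age and sex unbalanced. For waist circumference, continuous blood pressure, HbA1c and activity, any clinic difference in these characteristics that predicts change given baseline goes into the effect estimate. For BMI z-score the exposure is limited to pubertal timing and is probably small: about 4% to 7% of the planning change under a 0.5-SD imbalance, correlations of 0.2 to 0.4 and the plan's SD of 0.02. The actual size cannot be computed from the documents for any outcome.

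This rests on two readings: that children are analysed on BMI z-score rather than on percent change in weight or BMI, and that maturity is collected at baseline. The article schedules baseline measurements without listing them. If percent change were applied to children, that outcome would join the unstandardised group.

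**What to change.** State in the analysis paragraph that baseline maturity enters every child model as a pre-specified covariate, with age and sex added for outcomes not standardised for them. Say how the breast/genital and pubic hair ratings are combined into one score, confirm that the score is taken at baseline, and say how a missing score is handled. Describe maturity as a covariate, apart from the secondary behavioral outcomes. Add that the adjustment removes one measured component only and does not resolve the confounding of treatment with clinic.

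The cost is a few sentences and no new instrument. The downside is about three child-level degrees of freedom if each covariate is a single term (more if stage is categorical), plus possible missing self-reported stage data, which would drop children from the model unless handled.

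### The week-26 between-arm difference compares two treated arms, yet the plan calls it an intervention effect and may pool it with the week-13 effect

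*Protocol article*

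**What the plan says.** All of the following is in Methods/design of the protocol article, under Evaluation of the EPIC El Rio Families Study.

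- **Design.** For the first arm, "intervention participants will begin the 13-week face-to-face group program immediately". After 13 weeks, "the intervention participants will transition to a follow-up phase while the wait-listed controls will begin the intervention".
- **Primary outcome.** "The primary outcome is percent change in body weight and BMI at 13 weeks (post-intervention) and 26 weeks (follow-up/weight maintenance".
- **Model.** The analysis is "a mixed-model analysis of covariance including treatment group, time, and baseline value of the outcome", which "will be used to assess the effects of intervention at 13 and 26 weeks". No term for exposure or crossover is named.
- **Pooling rule.** The time-by-treatment interaction is examined first. "If there is no interaction effect, the overall treatment difference will be assessed"; otherwise the difference is reported at each visit. No significance level is given for this step.
- **First-pass t-tests.** "Initial analyses will compare the changes between baseline and follow-up", between the two arms, without naming the visit.

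The same section says that the design allows pre/post, intervention-versus-control and maintenance effects to be studied, and that the pilot is meant to provide estimates for a larger trial.

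**The concern.** The programme lasts 13 weeks and the wait-list arm starts it after week 13, so that arm is finishing it at about week 26. The other arm is then some 13 weeks past its own programme. Week 13 is the only visit at which one arm is treated and the other is not. A week-26 difference near zero would be expected from a programme that works equally well in both arms and is maintained, yet under the stated wording it would be read as no intervention effect at 26 weeks.

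The pooling rule adds a second problem. A programme that works, followed by crossover, itself produces a time-by-treatment interaction. Failing to detect that interaction in a small trial is no evidence that the two visits estimate the same quantity, but the rule then averages them.

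The consequence falls on what the pilot is for. Required sample size varies as 1/effect², so an estimate at half its true size would imply (1/0.5)² = 4 times the sample for the next trial, or might lead to the programme being dropped.

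**Working it through.** **Inputs from the article (sample-size paragraph, mothers).** Effect 6.0 points of percent weight, SD 4.0, 3 groups of 10 dyads per arm (30 versus 30), intra-group correlation 0.15, two-sided 0.05.

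**Assumed, not in the article.** The correlation ρ between the 13- and 26-week changes; a 0.05 level for the interaction test; equal SD at both visits; the share r of the effect retained by the intervention arm at week 26; the share g gained by the wait-list arm by then.

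**Step 1: the plan's own power figure.** Design effect = 1 + 9 × 0.15 = 2.35. SE = 4 × √(2 × 2.35/30) = 1.583. Then 6/1.583 = 3.79, which gives power of 96.6% (normal) or 80.6% (t with 6 − 2 = 4 df). Both agree with the stated figure of more than 80%. This is the power of a single treated-versus-untreated contrast, which only week 13 supplies.

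**Step 2: what pooling estimates.** Week-13 contrast = D. Week-26 contrast = (r − g)D. The pooled estimate is their mean, D(1 + r − g)/2.

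| r | g | Week-26 contrast | Pooled/D |
|---|---|---|---|
| 1 | 1 | 0 | 0.50 |
| 1 | 0.5 | 0.5D | 0.75 |
| 0.75 | 1 | −0.25D | 0.375 |
| 0.5 | 1 | −0.5D | 0.25 |

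With equal variances at the two visits, the average and the difference of the visits are uncorrelated (the covariance is Var13 − Var26 = 0). Conditioning on a non-significant interaction therefore does not remove the dilution.

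**Step 3: how often pooling would follow (r = g).** The interaction contrast is D − 0 = D, with SE = 4√(2(1 − ρ)) × √(2 × 2.35/30). This is 1.583 at ρ = 0.5 and 1.226 at ρ = 0.7. The chance of a non-significant result, normal to 4-df t:

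| D | ρ = 0.5 | ρ = 0.7 |
|---|---|---|
| 6 | 3% to 19% | 0.2% to 5% |
| 3 | 53% to 69% | 31% to 54% |

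At ρ = 0.9 and D = 3 the range is 1% to 12%.

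These figures apply the full design effect to the difference between visits, so they do not assume that group effects persist. If group effects do persist from week 13 to week 26, they cancel in that difference and the design effect for the interaction is 1. At D = 3 the ranges then fall to 17%–41% (ρ = 0.5) and 4%–20% (ρ = 0.7). At D = 6 they are at most about 1%.

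**Step 4: power of the pooled contrast at D = 6, r = g.** The expected value is 3.0, with SE = 4√((1 + ρ)/2) × √(2 × 2.35/30), which is 1.371 at ρ = 0.5 and 1.543 at ρ = 0.9. Power is 59% to 49% (normal) or 39% to 32% (t), against 96.6% or 80.6% at week 13.

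**The case against.** **Frequency.** The strongest reply is that dilution is conditional and, at the planning effect, uncommon. At 6 points the interaction would be found in at least about 80% of trials and the week-13 estimate reported separately. Averaged over both branches (4-df test), the rule returns about 5.6, 5.9 and 6.0 at correlations 0.5, 0.7 and 0.85, against a true 6. At an assumed 4 points it returns 3.2, 3.5 and 3.9. The article does not name a 4-df test either. An individual-level interaction test on the same clustered data would miss a 4-point effect in only 10.5%, 2.4% and 0% of trials, although such a test has a clustering problem of its own. This stands: a reader might infer that the trial will usually report half the effect, and the document does not support that. Smaller effects remain possible, because the 6.0% is an observed 6-month change from an earlier study and no control-arm change is given.

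**Mitigating text.** The abstract places the evaluation within a 13-week group randomised trial, and the design text lists maintenance separately from intervention versus control. Both suggest the right intent. Neither cancels the analysis paragraph, which states a between-arm effect at both visits and a rule for combining them. Intention-to-treat preserves assignment; it does not turn a treated arm into an untreated control.

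**The t-tests.** One might read the follow-up in the first-pass comparison as week 26, since the outcome paragraph attaches that word to "at 13 weeks (post-intervention) and 26 weeks (follow-up/weight maintenance". It may equally be the generic term for any post-baseline measurement. It is an ambiguity, not an error.

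**Sign reversal.** Regain in the intervention arm could make the week-26 difference favour the wait-list arm, as the last two rows of the first table show. No regain figure is in the article, and the optional booster sessions might limit regain, so this is a possibility only.

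**Conclusion.** The point holds as a defect in the stated analysis. That the week-26 contrast is immediate versus delayed treatment follows from the text alone and needs no numerical assumption. The mislabelling remains whichever branch of the interaction rule is taken.

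The dilution is real but conditional. It is one half when both arms have equal, maintained benefit, and about 0.25 to 0.75 under the other scenarios tabulated. The chance of pooling is about 0–19% at the planning values. It is about 31–69% at 3 points with correlations of 0.7 to 0.5, and lower if group effects persist between visits or the correlation is higher. These frequencies rest on an assumed effect, correlation and test.

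Under equal benefit the error is toward the null, so it does not manufacture efficacy. This point does not impugn the week-13 comparison. The arithmetic is for mothers' weight; the logic applies equally to the children's BMI z-score and to the secondary outcomes measured at both visits.

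**What to change.** - Make the week-13 between-arm difference the sole estimate of intervention versus control, not conditional on any interaction test.
- Delete the rule that reports one overall difference across 13 and 26 weeks.
- State that the first-pass t-tests use change from baseline to week 13.
- Use week-26 data for within-arm maintenance in the intervention arm (weeks 13 to 26, noting the optional boosters) and for pre/post change in the wait-list arm. Call the latter descriptive, because it has no concurrent untreated control.
- If a week-26 between-arm contrast is kept, label it immediate versus delayed treatment.

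The change is to wording only and needs no new data. Its cost is the claim of a between-arm intervention effect at 26 weeks.
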